### Recruitment procedures {15}

Pregnant women who are diagnosed with GDM by the OGTT will be asked to undergo nutritional assessment at the nutrition clinic. After assessment, women who are potentially eligible to participate in our trial will be given a study flyer. At the same time, our principal investigator ([name]) will explain the detailed information of the trial and screen for eligibility. The scientific value of this study and the potential benefits it may bring to patients will also be fully explained to potential participants to enhance their motivation for enrollment.

### Informed consent procedures {26a}

All participating patients will sign a written informed consent form. The principal investigator ([name]) will explain the study’s purpose to the patients and obtain their written informed consent before they participate.

### Consent or assent: ancillary studies {26b}

We did not plan to collect participants’ data and biological specimens for ancillary studies.

### Allocation: sequence generation {16a}

Eligible patients will be randomized into three groups: The nutrition education group (*n* = 45, accept nutrition education of GDM), fiber group 1 (*n* = 45, receive nutrition education of GDM plus 12 g/day mixed soluble fiber, which contains 2 g of XOS and 10 g of inulin), and fiber group 2 (*n* = 45, accept nutrition instruction of GDM plus 24 g/day mixed soluble fiber, which contains 4 g of XOS and 20 g of inulin). Simple randomization with a 1:1:1 allocation ratio will be performed using a computer-generated random number sequence.

### Allocation: concealment mechanism {16b}

The allocation sequence will be concealed from those assigning patients to the intervention groups using opaque sealed envelopes.

### Allocation: implementation {16c}

An independent coordinator, who have no contact with participants, will generate a random value for each participant, shuffle the order based on random number sequence, and then assign them sequentially to one of three groups using numbered, opaque, sealed envelopes. Team investigators will access individual assignments by opening envelopes only after written consent is obtained. This method ensures a completely random and fair distribution.

### Outcomes {12}

The primary outcome measure will be the Change in GSP after 8 weeks of treatment across the different groups. GSP is a sensitive indicator of blood glucose levels in the last 3 weeks, making it particularly useful for monitoring pregnant women with diabetes. According to Morris et al., GSP levels correlate strongly with short-term glycemic control (fasting glucose: *r* = 0.798; postprandial: *r* = 0.846) and are measured via affinity chromatography targeting glycated serum proteins. This method allows frequent assessment of diabetic control, addressing the need for rapid treatment adjustments during pregnancy [20]. Secondary outcomes include fasting plasma glucose, 2 h-PPG, FINS, HbA1c, TC, LDL-C, HDL-C, TG, Wexner constipation score (WCS), the Bristol Stool Form Scale (BSFS), pregnancy outcomes, and changes in gut microbiota. Fasting venous blood will be collected at baseline (week 0), week 4, and trial completion (week 8). Blood samples will be processed within 2 h of collection (30-min room-temperature clotting, centrifugation at 3000 × g for 15 min), with serum/plasma aliquots stored at −80 °C. The Clinical Laboratory Department of Qingdao Municipal Hospital will test all the above laboratory indicators.

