### Explanation for the choice of comparators {6b}

To determine whether a dose–response relationship exists between the dose of XOS inulin and blood glucose metabolism, two supplement doses, 12 g/day and 24 g/day, will be used in the two experimental groups.

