### Objectives {7}

We hypothesize that daily XOS-inulin supplementation improves glycolipid metabolism in GDM patients via modulation of gut microbiota. We designed this trial to test the efficacy of daily XOS inulin supplementation after the diagnosis of GDM for improving glycolipid control and changing the gut microbiome compared with standard dietary education. We also want to study the effects of XOS inulin supplementation on pregnancy outcomes.

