### Trial design {8}

This study is an 8-week, parallel design, open-label, three-arm, single-center randomized controlled superiority trial. The participant flow through the trial is described in Fig. 1. The study protocol was designed and developed in accordance with the Standard Protocol Items: Recommendations for Interventional Trials (SPIRIT) 2013 checklist [15] (see Additional file 1). This trial was registered in the Chinese Clinical Trial registry: ChiCTR2200060117 (May 19, 2022).

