### Statistical analysis {20a}

Statistical analyses will be performed using the R 4.3.0 software. The Shapiro–Wilk test will be used to check for a normal distribution of the data. Continuous variables with a normal distribution will be presented as the mean (standard deviation [SD]); non-normal variables will be reported as the median (interquartile range [IQR]). Categorical data will be compared among the three groups using chi-square tests and partitions of the chi-square method. Linear models will be used to compare the mean values of the outcome variables among the three groups, adjusting for baseline values (e.g., age, BMI, nationality, gestational weeks, calorific intake). GSP Changes from baseline to week 8 will be analyzed using mixed-effects models with treatment group, time, and group × time interaction as fixed effects, adjusting for baseline GSP. *P*-value of less than 0.05 will be considered statistical significance. Post hoc pairwise comparisons were adjusted using the Bonferroni method to reduce the probability of type I error.

We will evaluate gut microbial diversity through complementary alpha- and beta-diversity analyses. For alpha diversity (within-sample microbial complexity), we will calculate three complementary metrics: Chao1 index (quantifying species richness), Shannon index (reflecting both richness and evenness), and Simpson index (measuring dominance of abundant species). Alpha-diversity differences between groups will be assessed using the Wilcoxon test. The cross-sectional difference in beta diversity (between-sample compositional differences) between the groups will be assessed by permutational analysis of variance (PERMANOVA) of Bray–Curtis dissimilarity and illustrated by PCoA models [35]. The significant bacterial taxa responsible for discrimination between the three groups will be identified via linear discriminant analysis (LEfSe) with linear discriminant analysis (LDA) [36]. Some multiple comparisons, such as differential abundance analysis of the microbiota, will be corrected using the Benjamini–Hochberg false discovery rate (FDR).

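### The primary GSP comparison is stated across three groups, while the objective and sample size rest on fiber versus education, which appears only as a Bonferroni-adjusted post hoc pair

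*Protocol article*

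**What the plan says.** Five places in the protocol bear on which comparison decides the trial.

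- Trial design {8} describes a "three-arm, single-center randomized controlled superiority trial", without saying which arm must be superior to which.
- Objectives {7} sets XOS inulin, with the doses not separated, against education: "improving glycolipid control and changing the gut microbiome compared with standard dietary education".
- Explanation for the choice of comparators {6b} gives the reason for two doses: "To determine whether a dose–response relationship exists between the dose of XOS inulin and blood glucose metabolism".
- Outcomes {12} states the primary comparison: "The primary outcome measure will be the Change in GSP after 8 weeks of treatment across the different groups".
- Statistical analysis {20a} analyses GSP with "mixed-effects models with treatment group, time, and group × time interaction as fixed effects, adjusting for baseline GSP", uses P below 0.05, and adds: "Post hoc pairwise comparisons were adjusted using the Bonferroni method to reduce the probability of type I error". It does not give the number of pairs, or say which model term or contrast is decisive.

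Sample size {14} takes an HbA1c difference of 0.27% between one inulin dose and control, and arrives at 37 per group for 90% power at alpha 0.05. With an allowance for dropout this becomes 45 per group, 135 in all.

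**The concern.** The question the trial asks is whether fiber improves on education. The comparison written down as primary is a three-group one. A three-group test can be significant because the two doses differ from each other, which says nothing direct about benefit over education. The two contrasts that do answer the objective come last in the analysis section. If all pairs are adjusted, they also share alpha with 24 g versus 12 g.

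Two things are at stake. A result could be reported as the primary finding although neither dose beats education. And the comparison that matters would be tested at a stricter level than the one used for sizing, so the stated 90% power would not apply to it.

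**Working it through.** **1. The plan's own figure.** For two means, n per arm = 2(z₁₋α/₂ + z₁₋β)² / d². No SD is given, so 37 cannot be reproduced independently, only solved backwards (two-sided alpha assumed):

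- d = √[2 × (1.960 + 1.282)² / 37] = √(2 × 10.51 / 37) = 0.754, an implied HbA1c SD of 0.27 / 0.754 = 0.358.
- With the t distribution in place of the normal, 90% at 37 per arm needs d of about 0.765.

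Either way, 37 per arm is the size for a single two-group contrast at the full 0.05. Carrying this effect from HbA1c to GSP is an assumption.

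**2. Power of dose versus education after Bonferroni.** Power = Φ(d√(n/2) − z₁₋α/₂), with d√(37/2) = 0.7536 × 4.301 = 3.241:

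| Adjustment | Alpha per test | Power | n per arm for 90% |
|---|---|---|---|
| None | 0.05 | Φ(3.241 − 1.960) = 90% | 37 |
| Two pairs | 0.025 | Φ(3.241 − 2.241) = 84% | 44 |
| Three pairs | 0.0167 | Φ(3.241 − 2.394) = 80% | 48 |

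Under the three-pair reading, 90% would need 48 analysed per arm, more than the 45 to be randomised.

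**3. How often the three-group test is positive without either dose beating education.** Simulation: 37 per arm, normal data, pooled variance, two-sided tests, three-group F test at 0.05, pairs at 0.05/3.

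| True pattern | Effect 0.765 | Effect 0.5 |
|---|---|---|
| Both doses fully effective | about 2% | about 4% |
| 12 g half as effective | about 3% | about 5% |
| 12 g inert | about 12% | about 18% |

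At effect 0.765, 24 g versus 12 g is the only significant pair in about 0%, 0.9% and 10% of trials in the same three patterns.

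**4. Can the pairs be tested with less loss?** With three arms, any two of the three pairwise null hypotheses together imply that all three means are equal. The only intersection hypothesis is therefore the global one. Testing it at 0.05, and then each pair at 0.05, is a closed procedure. In simulation the chance of any false pairwise claim under the global null was 5.0%. Power at effect 0.765:

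| True pattern | Dose | Bonferroni, three pairs | Bonferroni, two pairs | Closed test |
|---|---|---|---|---|
| Both fully effective | each | 80% | 84% | 88% |
| 12 g half as effective | 24 g | 80% | 84% | 83% |
| 12 g inert | 24 g | 80% | 84% | 88% |

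**The case against.** The other side has a good case, and much of it stands.

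- *The rule may be written elsewhere.* Data management {19} lists a statistical analysis plan that is not shown, and this is a journal article. A reader might infer that the success rule is open to choice after the results are seen. The document does not establish that. What remains is that the protocol does state a primary comparison, and it does not match the objective and the sizing.
- *Error control is in place.* A reader might infer an inflated false-positive rate. The Bonferroni sentence prevents that for the pairwise comparisons.
- *The procedure is an ordinary one.* An overall test followed by adjusted pairs is the natural reading, and post hoc often just means follow-up pairs. This stands, but it leaves open whether the overall test alone counts as success.
- *The plausible readings mostly agree.* The overall test and an either-dose rule give the same answer in all but about 2–3% of trials when both doses work. When they part because 12 g is inert, the overall test is still a true positive: the groups do differ. A much larger conflict appears if both doses are required to succeed, but no section suggests that rule. With a dose–response aim, different results by dose are to be expected, so that comparison is not used here.
- *24 g versus 12 g has a purpose.* It serves the aim in {6b} and should be kept, as a secondary comparison.

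**Conclusion.** The point holds as a mismatch within the protocol. The primary outcome is framed across three groups, whereas the objective and the sample size are framed as fiber versus education. It is neither a failure of type I error control nor proof that no success rule exists.

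The risk of a primary result without benefit over education is small if both doses work (about 2–3% at the assumed effect, 4–5% at an effect of 0.5). It is about 12% at the assumed effect if 12 g is inert. The steadier cost is power: about 80% per dose instead of 90% if three pairs are adjusted.

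These figures assume 37 analysed per arm, two-sided tests, an effect solved backwards from the HbA1c sizing and carried to GSP, and, where stated, three adjusted pairs. The mismatch itself depends on none of them. The change should be made, because it is cheap and gives a better test of the stated objective.

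**What to change.** In Outcomes {12} and Statistical analysis {20a}:

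1. Name two primary contrasts from the GSP model at week 8: 12 g versus education and 24 g versus education.
2. State that efficacy is claimed separately for each dose that passes, and that the three-group test alone supports no efficacy claim.
3. Label 24 g versus 12 g as a secondary comparison serving the dose–response aim.
4. Replace Bonferroni with closed testing: pairs at two-sided 0.05 only if the three-group week-8 test is significant.

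A simpler alternative to item 4 is Bonferroni over the two primary contrasts only, at 0.025 each, with about 84% power per fully effective dose. It does about as well as closed testing when 12 g is half as effective, and less well in the other two patterns examined.

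The cost is a few sentences and no extra data or participants. There are two downsides: closed testing has no simple matching set of simultaneous confidence intervals, and the sponsor gives up any freedom to choose the reading later. If the separate analysis plan already names the contrasts, the protocol text should be brought into line with it.

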### Demographics and anthropometric measurements

We will collect information on demographic and anthropometric measurements, including date of birth, age, home address, telephone number, gestational age, height, weight, and body mass index (BMI). Blood pressure and heart rate tests will be conducted via an electronic blood pressure monitor. After the participants void their bladders and remove their heavy clothes and shoes, trained investigators perform a height and weight measurements via a studio meter and an electronic weighing scale. Participants will report their weight before pregnancy. BMI is calculated with an equation that incorporates height and weight: weight (in kg)/height^2^ (in m^2^) [21].

### FFQ and physical activities

To assess food and nutritional intake before and during the intervention period, experienced dietitians will Help participants complete the FFQ on day 0 and weeks 4 and 8. This questionnaire is a reasonably reliable and valid tool for assessing the food and nutrient intakes of urban pregnant women in Central China and consists of 10 food groups: cereals, meats, fish, eggs, beans, vegetables, fruits, nuts, milk or milk products, and beverages [22]. This tool requires participants to recall their usual frequency of intake and portion size during the past 4 weeks. Dietitians use color food photography atlas with different food portion sizes and food models to provide accurate estimate. After collecting the primary data, the daily nutrient intakes will be calculated based on the China Food Composition Database [23]. Participants will be asked about types and frequency of sports they play. Participants will be also recorded the average amount of time spent doing housework every day. The average walking time every day when they are on the way to and from work, working, shopping, and hanging out will also be recorded.

## Biological specimen collection, analysis, and storage

### Constipation assessment

Constipation is a common sign in GDM patients, and the outcomes from this trial may be beneficial for alleviating this disorder. Two scales, the Wexner constipation score (WCS) and the Bristol Stool Form Scale (BSFS), are used to assess the severity of constipation and measure stool form [24, 25]. The WCS is a Likert scale that includes eight items: the frequency of bowel movements, difficulty, completeness, pain, time, assistance, failure, and history. Based on the grading of the scale, scores range from 0 (normal) to 30 (severe), and a score of 15 is the cut-off point [26]. The BSFS is a 7-point scale for classifying stool forms into seven categories: separate hard lumps, such as nuts (hard to pass); sausage-shaped but lumpy; similar to sausage but with cracks on its surface; soft blobs with clear-cut edges (passed easily); fluffy pieces with ragged edges, a mushy stool; and watery, no solid pieces (entirely liquid) [25]. These two scales are widely used worldwide in clinical and research settings by doctors, researchers, and patients. Investigators will complete questionnaires based on the latest defecation status of the participants during three visits (weeks 0, 4, and 8).

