### Data collection plan {18a}

Figure 2 shows the baseline and follow-up measurements and a summary of the data. The participant’s follow-up is scheduled for weeks 0, 4, and 8. In weeks 0 and 4, dietary fiber products were dispensed depending on the intervention groups. After obtaining informed consent, baseline assessments will be conducted, including demographics, gestational age, anthropometrics, blood pressure, and heart rate. During this visit, participants will have the first blood test (GSP, fasting glucose, fasting insulin (FINS), 2-h postprandial plasma glucose (2 h-PPG), HbA1c, total cholesterol (TC), LDL cholesterol (LDL-C), HDL cholesterol (HDL-C), and triglycerides (TG)). Trained dietitians will complete the study questionnaire, including a pregnant woman-specific food frequency questionnaire (FFQ), self-reported physical activities, the Wexner constipation score (WCS), and the Bristol stool chart. The same questionnaires and blood tests will be conducted at the second (week 4) and third (week 8) visits. Stool samples will be obtained from participants at every visit to analyze gut microflora colonization patterns. After delivery, information on maternal pregnancy outcomes and neonatal outcomes will be acquired through telephone calls and electronic medical system at the hospital. At 6-week postpartum, we will continue to collect maternal OGTT results and infant growth/feeding data through telephone follow-ups.

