One strength of this proposed study is that it may be the first clinical trial to examine the therapeutic effects of daily XOS inulin supplementation on pregnant women diagnosed with GDM. Two different dose groups and gut microbiota analyses are also considered strengths of this study. There are also several limitations of this study. First, women with gestational diabetes had an increased risk of developing type 2 diabetes compared with those who had a normoglycemic pregnancy [50], and the 8-week trial period cannot fully capture the long-term effects of XOS-inulin supplementation on glycemic control and pregnancy outcomes. Future studies with extended follow-up (e.g., postpartum or infant growth stages) are needed to evaluate sustained benefits, such as childhood obesity risk and type 2 diabetes mellitus after gestational diabetes. Second, as an open-label trial, the absence of a placebo group may introduce bias in participant-reported outcomes (e.g., constipation scores). Blinded designs could strengthen the validity of subjective measures. Third, the adherence was primarily monitored via self-report and product return counts, which may not fully reflect actual intake. Future trials should incorporate objective adherence markers (e.g., fecal XOS/inulin metabolites). Overall, all participants in this trial will be well-educated about GDM nutrition knowledge and behaviors, such as calculating meal energy values, understanding food nutrients, creating balanced meal plans, optimizing eating schedules, and breastfeeding/formula feeding best practices. We believe that our nutritional counselling will change their food habits and provide long-term health benefits [51].

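### The two bowel scales have no workable common recall period, and the protocol is inconsistent about who completes them in an open-label trial

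*Protocol article*

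**What the plan says.** **Basis for scoring.** The protocol article, section Constipation assessment, gives one rule for both scales: "Investigators will complete questionnaires based on the latest defecation status of the participants during three visits", at weeks 0, 4 and 8. It states no recall period. The same section lists the eight Wexner items as "the frequency of bowel movements, difficulty, completeness, pain, time, assistance, failure, and history".

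**Who completes the forms.** That section names investigators. In Data collection plan {18a}, "Trained dietitians will complete the study questionnaire", and the questionnaire set there includes the WCS and the Bristol chart. The Discussion treats the scores as coming from the participant: it says the lack of a placebo group "may introduce bias in participant-reported outcomes (e.g., constipation scores").

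**Knowledge of the arm.** Trial design {8} describes an "8-week, parallel design, open-label, three-arm, single-center randomized controlled superiority trial". Allocation: implementation {16c} adds: "Team investigators will access individual assignments by opening envelopes only after written consent is obtained".

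**Stool categories.** Constipation assessment states: "The BSFS is a 7-point scale for classifying stool forms into seven categories". Six descriptions follow.

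**Role of the scales.** Both are secondary outcomes in Outcomes {12}. Adverse events {22} uses a Wexner score of 15 or more that continues despite dietary measures as its definition of clinically significant constipation.

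**The concern.** A frequency, or a history, is a property of a period. A rule that points the rater to the most recent bowel status either conflicts with those items or leaves each rater to choose how far back to look. For the Bristol scale, the same rule allows a single stool to represent the state of the bowel at a visit, and visits are four weeks apart. Both faults add variation that has nothing to do with treatment. If raters choose different windows in different arms, they could also add bias.

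The rater matters because the trial is open-label. A woman's own expectation can already colour her answers. If a member of staff who knows her arm turns those answers into a score, a second expectation may enter. The Discussion concedes the first source but does not mention the second, since it regards the scores as participant-reported.

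At stake are two secondary outcomes, the stated aim of evaluating gastrointestinal function (Abstract, Discussion paragraph), and the constipation criterion in the safety section, which needs a score with a defined period behind it.

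**Working it through.** **1. Items against the scoring rule.** The Wexner description announces eight items and lists eight, so it is consistent in number. By the names the article gives them, at least three (frequency, failure, history) describe a pattern over time. There are two readings of the rule:

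| Reading | Wexner | Bristol |
|---|---|---|
| The most recent defecation | At least 3 of 8 items do not fit a single event | One stool represents the visit |
| Recent bowel habit | Scorable, but over a window each rater chooses | Scorable, but over a window each rater chooses |

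Neither reading gives a common window. By contrast, FFQ and physical activities sets a recall of the past 4 weeks for the food questionnaire at the same three time points.

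**2. Who completes the scales.**

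| Section | Who |
|---|---|
| Constipation assessment | Investigators |
| Data collection plan {18a} | Trained dietitians |
| Discussion | Scores described as participant-reported |

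That staff know the arm is an inference, but a firm one. The trial is open-label, the article describes no blinded assessor, and team investigators open the envelopes. Dietitians deliver the education (Interventions {11a}) and stay in contact with the women by WeChat (section {18b}).

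**3. Bristol list.** Announced: 7. Listed, counting the entries separated by semicolons: hard lumps; lumpy sausage; cracked sausage; soft blobs; fluffy or mushy pieces; watery. That is 6, so 7 − 6 = 1 is missing.

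**4. Illustrative size for the Bristol scale.** The article gives no reliability figure and no stool count, so both are assumptions: a within-woman reliability (ICC) of 0.3 to 0.5 for one stool, and k = 3 or k = 7 stools in a week. The variance of a mean of k stools relative to one stool is ICC + (1 − ICC)/k, and the standard-error ratio is its square root.

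| k | ICC | Variance ratio | SE ratio | SE reduction |
|---|---|---|---|---|
| 3 | 0.3 | 0.3 + 0.7/3 = 0.533 | 0.73 | 27% |
| 3 | 0.5 | 0.5 + 0.5/3 = 0.667 | 0.82 | 18% |
| 7 | 0.3 | 0.3 + 0.7/7 = 0.400 | 0.63 | 37% |
| 7 | 0.5 | 0.5 + 0.5/7 = 0.571 | 0.76 | 24% |

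The formula treats an ordinal score as continuous with independent errors. It applies to the score at one visit and compares averaging with a true single-stool score. A recalled usual form is not an exact average, so the gain from recall may be smaller. No comparable figure is available for the Wexner score or for rater bias.

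**The case against.** **The wording may mean current bowel habit.** The sentence speaks of a defecation status, not of one stool, and it follows a list that includes frequency and history. A reading under which the authors' own instrument could not be scored is the less charitable one. This stands in part: a reader might infer that the scales are scored from a single stool and nothing else, or that the Wexner score is impossible to obtain, and the text does not go that far. The looser reading still leaves the window undefined. The point is also not just a detail left to the form, because the article states a basis for scoring and that basis does not suit the items.

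**Open-label bias is already conceded.** The Discussion names constipation scores and says blinding would help. Staff may simply write down the woman's answers, as dietitians help with the FFQ, and investigators and dietitians may be the same people. All of this is possible. A reader might infer that staff rate independently of her account, or that a bias towards fibre is established. The documents show neither, and no size can be put on it. What remains is that three sections describe the source differently and that the concession does not cover staff completing the forms.

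**The missing Bristol category is a slip in prose.** This stands. The article cites the scale, calls it 7-point and refers to the chart. A reader might infer that a six-category form is in use and misclassifies stools. No document shows such a form.

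**The precision figures rest on assumptions.** This stands too. Seven stools a week is optimistic in a population for which the article calls constipation common, hence the k = 3 rows.

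**Conclusion.** The concern holds as a defect in how two secondary outcomes are measured. The scoring basis fails on either reading: it fits at least three of the eight Wexner items poorly, or it leaves the window to the rater. The three descriptions of who completes the scales conflict and need reconciling, and because staff can know the arm, the choice of rater matters. Expectation on the woman's side is acknowledged in the Discussion and would remain in any unblinded version.

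The size is modest and mostly unquantified. The 18–37% range across the four Bristol scenarios depends on the assumed reliability, the assumed stool count and the single-stool reading; the conclusion does not depend on it. The primary GSP outcome and the sample size are untouched. The Wexner-based adverse-event criterion is affected only in that its score lacks a defined period; nothing here bears on how such an event should be managed. The six-of-seven list is editorial. The change is worth making because it costs little, not because the trial's main conclusion is at risk.

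**What to change.** 1. In Constipation assessment, replace the present scoring basis with one fixed recall window per scale, identical in all three arms and at weeks 0, 4 and 8. For example, use the past 4 weeks for the WCS, matching the FFQ, and the usual stool form over the past 7 days for the BSFS. Recall is enough, and no new diary is needed. The daily calendar in Strategies to improve adherence {11c} is described as an adherence record and should not be assumed to hold stool data.
2. Have the woman complete both scales herself before she meets the dietitian or investigator at each visit.
3. Reconcile Constipation assessment, Data collection plan {18a} and the Discussion, so that all three name the same person as completing the scales.
4. Editorial: list all seven Bristol categories and confirm that the form in use has seven.

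**Cost.** Wording changes to the protocol and questionnaire, and a few minutes of self-completion per visit, with no extra visits or staff. Recall over a window brings some recall error, and self-completion removes only the staff layer of expectation, not the participant's own.
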